## Abstract

**Background:**

High-quality chest compressions are essential for effective cardiopulmonary resuscitation (CPR), but novice nurses often struggle with maintaining the right compression rate, depth, and recoil. Simple tools like metronomes can help improve cardiopulmonary resuscitation quality by providing a steady rhythm for better performance.

**Objective:**

The objective is to evaluate whether metronome-guided CPR improves the quality of chest compressions performed by novice nurses in a simulated setting

**Method:**

This single-centric study of a simulation-based randomized controlled trial consists of 160 novice nurses divided equally into intervention and control groups (80 each).

Both groups performed a pre-test consisting of a 2-minute compression-only CPR session on a Q-CPR manikin without metronome guidance. After a 20-minute rest interval to prevent fatigue, the intervention group performed another 2-minute compression-only CPR session using a metronome set at 110 compressions per minute delivered. The control group repeated the CPR session under standard conditions without metronome assistance.

**Expected outcome:**

This study hypothesizes that novice nurses using a metronome throughout simulated cardiopulmonary resuscitation will achieve significantly higher quality chest compressions compared to those who do not use a metronome. It is expected that metronome-guided cardiopulmonary resuscitation will enhance the accuracy, depth, and consistency of compressions.

## Specifications table

**Table utbl0001:** 

**Subject area**	Medicine and Nursing
**More specific subject area**	Nursing education, Critical care
**Name of your protocol**	Metronome assisted CPR training for community based nursing education
**Reagents/tools**	• Q-CPR Manikin (used to simulate adult CPR) • Resusci Anne wireless skill reporter software (Integrated with the manikin • Metronome (provided auditory guidance during chest compressions) • Personal computer/ Laptop (To run the skill reporter software)
**Experimental design**	Randomized controlled trials (block randomization) with 1:1 allocation between intervention and control groups. **Intervention group:** Participants allocated to the intervention group underwent **metronome-guided cardiopulmonary resuscitation (CPR)**. Initially, all participants completed a **baseline (pre-test)** consisting of a 2-minute session of compression-only CPR on a Q-CPR manikin without any auditory guidance. Following a standardized **20-minute rest period** to minimize fatigue effects, participants in the intervention group performed a **post-test 2-minute compression-only CPR session** with **metronome assistance set at 110 beats per minute (BPM),** delivered via a mobile phone application. **Control group:** Participants in the control group followed the same **study timeline and testing protocol** as the intervention group, ensuring methodological consistency. They completed a **2-minute pre-test compression-only CPR session** on the Q-CPR manikin without metronome guidance, followed by a **20-minute rest interval**. During the **post-test,** control group participants performed another **2-minute compression-only CPR session under standard conditions,** without any auditory or feedback assistance.
**Trial registration**	This study was registered in Clinical Trial Registry of India (CTRI). The trial registration number is: CRTI/2024/05/067872.
**Ethics**	This study was conducted at the Simulation Lab of a tertiary care centre of the Sri Ramachandra Institute of Higher Education and Research (Deemed to be university) hospital following the Declaration of Helsinki and was approved by the institutional review board of the same institution (reference code: CSP/23/AUG/134/754, dated October 16, 2023). Written informed consent was obtained from the participants.
**Value of the Protocol**	Ensures **methodological rigor and transparency** by clearly defining standardized procedures for intervention delivery, outcome assessment, and data analysis, thereby minimizing bias and enhancing reproducibility. Enables **objective evaluation of metronome-guided CPR** by systematically comparing intervention and control groups under identical simulated conditions. Provides a **replicable and scalable framework** for CPR training research, supporting evidence-based integration of low-cost tools like metronomes into nursing education and clinical practice.

## Background

Cardiac arrest, a critical medical emergency, necessitates an immediate and efficacious intervention to enhance the likelihood of survival. Cardiopulmonary resuscitation (CPR), an emergency medical technique, involves healthcare professionals administering chest compressions and artificial respirations to manually sustain cerebral function until advanced interventions can be implemented to re-establish spontaneous circulation and respiration in a patient experiencing cardiac arrest [1]. Consequently, medical personnel, encompassing physicians, nurses, and paramedics, must possess the capability to execute cardiopulmonary resuscitation as a core competency [2]. Nurses, as primary healthcare professionals, are crucial first responders; therefore, their expertise, abilities, and assurance in cardiopulmonary resuscitation are vital for preserving life [3]. Current guidelines stipulate that high-quality chest compressions are characterized by an optimal frequency of 100–120 compressions per minute (CPM), a compression depth of 50–60 mm, and complete chest recoil following each compression. This approach to chest compressions facilitates the most effective perfusion pressure and increases the probability of spontaneous circulation restoration [4].

Conversely, the attainment of a standardized and efficacious cardiopulmonary resuscitation (CPR) application presents a persistent difficulty, stemming from variations in technique, disparities in the experience of providers, and the inherently high-stress environment of resuscitation situations, even among healthcare professionals [5]. Furthermore, factors including fatigue, insufficient training, and emotional strain can adversely affect CPR performance, potentially influencing patient outcomes. To mitigate these obstacles and to augment CPR competency, novel pedagogical approaches, such as simulation-based training, have garnered increasing attention for their efficacy in improving nursing students' skills and fostering knowledge retention [6,7].

Metronome guidance offers a straightforward and cost-effective approach to enhancing cardiopulmonary resuscitation (CPR) techniques. This method delivers a consistent auditory cue, producing a steady beat at a specific tempo, quantified in beats per minute (BPM). Musicians frequently employ metronomes to maintain a uniform rhythmic pattern during performance [8]. In a comparable manner, a metronome can be programmed to the pre-established compression rate, serving as a reference point to assist rescuers in maintaining a consistent rhythm and pace throughout chest compressions. To our knowledge, this investigation represents the initial application of metronome-guided CPR training for novice nurses within a tertiary care hospital setting. Consequently, the study holds the potential to yield significant insights regarding the influence of metronome guidance on the quality of chest compressions during simulated CPR scenarios. The objectives of the study were to•To assess the quality of chest compression during simulated cardiopulmonary resuscitation among novice nurses.•To evaluate the efficacy of the metronome on the quality of chest compression during simulated cardiopulmonary resuscitation among novice nurses.

## Description of protocol

### Study design

This was an open-label, two-arm, randomized controlled, single-center study performed in the Simulation Lab of a tertiary care university teaching hospital from November 2023 to March 2024. The trial protocol for this investigation was registered prospectively on May 24, 2024, with the Clinical Trial Registry of India (CTRI) under the registration number CTRI/2024/05/067872. Additionally, approval was secured from the Institutional Ethics Committee of Sri Ramachandra Institute of Higher Education and Research (Deemed to be University), Chennai (reference code: CSP/23/AUG/134/754, dated October 16, 2023), and all procedures conformed to the principles outlined in the Declaration of Helsinki. All participants provided informed and written permission.

### Study settings, participants, and recruitment

The novice nurses were recruited in a tertiary care hospital of a multidisciplinary university. Before completing the written consent form, participants who satisfied the eligibility requirements obtained a thorough explanation of the study. Participants' eligibility criteria were as follows:

#### Inclusion criteria

•Novice nurses aged within 25 years.•Novice nurses with basic cardiopulmonary resuscitation training.•Those who are physically capable of performing chest compressions as per cardiopulmonary resuscitation guidelines.•Novice nurses who have experience of less than 1 year.

#### Exclusion criteria

•Physicians, residents, and other healthcare professionals other than nurses were excluded.•Those with medical conditions or physical limitations that may prevent them from safely performing chest compressions (musculoskeletal disorders, cardiovascular conditions, neurological deficits, pregnancy).•Participants who fail to provide informed consent or withdraw from the study before completion.

### Sample size

Referring to the previous study, Use of a Metronome in CPR: A Simulation Study [9], the estimated sample size was determined to be 160 participants; this would achieve the power of 80% at a level of significance of 0.05. The calculated sample size per group is 72. Accounting for a 10% dropout rate, the adjusted sample size is 80 participants per group, resulting in a total of 160 participants in both the intervention and the control group. The Minimal Clinically Important Difference (MCID) of 22 compressions per minute for compression rate was derived from previous studies that evaluated performance variability during CPR training between the experimental group and the control group. Prior research using simulation-based assessments identified a change of approximately 20–25 compressions per minute as the threshold at which differences in performance become clinically relevant and perceptible in terms of resuscitation quality [10,11]

### Randomisation, allocation concealment, and blinding

A total of 180 participants were assessed for eligibility, and 20 were excluded (12 did not meet the inclusion criteria, and 8 declined to participate). The remaining 160 participants were enrolled in the study. The flow of participants through the study is presented in Fig. 1 (CONSORT flow diagram). A block randomization was utilized to ensure balanced allocation of participants between the intervention and control groups. The total sample was separated into 16 blocks, with each block containing 10 participants—5 assigned to the study group (metronome-assisted CPR) and 5 to the control group (standard CPR without metronome guidance). This approach was chosen to maintain equal group sizes throughout the enrollment process and to minimize potential biases.

**Fig. 1 fig0001:**
[figure not shown]
CONSORT flowchart illustrating the stages of participant recruitment, allocation, follow-up, and analysis in the randomized controlled trial.

Allocation concealment was achieved using a sealed envelope block randomization method. Opaque, sequentially numbered envelopes containing the group assignments were prepared in advance and mixed thoroughly. As each participant enrolled in the study, they were asked to select a sealed envelope, which determined their group allocation. This method ensured that neither the participants nor the researchers could predict group assignments prior to randomization, thus reducing selection bias.

### Intervention and data collection

Following randomization, all participants did a 2-minute pretest of compression-only cardiopulmonary resuscitation on a Q-CPR manikin without any metronome guidance. This pretest was conducted to establish a baseline measurement of chest compression quality for both groups under identical conditions. Data for each participant was recorded using the Q-CPR manikin, connected to the Resusci Anne Wireless Skill Reporter software and a personal computer skill reporting system (Laerdal Medical AS, Stavanger, Norway). After a 20-minute rest interval, to prevent fatigue from affecting post-test performance, the intervention group performed a 2-minute compression-only CPR session on the QCPR manikin, this time guided by a metronome set to 110 beats per minute (BPM), delivered through a mobile phone application. In contrast, the control group completed the post-test without any metronome assistance, replicating standard CPR practice.

The system measured key CPR quality indicators, focusing on three core components: adequate chest compression depth, compression rate, and full chest recoil. In addition to these specific metrics, the software generated an overall performance score based on each participant’s adherence to CPR guidelines. This ensured an accurate and objective assessment of CPR quality, providing consistent data for evaluating the impact of metronome guidance on chest compression performance.

To ensure objective evaluation, both groups underwent a post-test assessment measuring key CPR performance indicators, including compression rate, depth, and recoil. While full blinding of participants was not feasible due to the audible metronome in the study group, efforts were made to blind the data analysts to group assignments during the evaluation phase to minimize assessment bias.

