### Outcome measures

The primary outcome measures focused on evaluating the quality of chest compressions performed during cardiopulmonary resuscitation (CPR). These included:

Compression Rate: Measured in compressions per minute (cpm), with an optimal range defined as 100–120 cpm according to American Heart Association (AHA) guidelines.

Compression Depth: Recorded in millimeters, assessing whether compressions met the recommended depth of 51–61 mm.

Chest Recoil: Evaluated based on the proportion of compressions allowing complete chest recoil, important for effective blood flow during CPR.

Overall CPR Quality Score: The overall CPR quality score was automatically generated by the Q-CPR skill reporter system integrated with the Resusci Anne manikin. The software calculates a composite score (ranging from 0 to 0–100%) based on real-time assessment of four key parameters: compression rate, compression depth, recoil, and hand position accuracy. Each parameter contributes proportionally to the total quality score according to the system’s internal algorithm, which follows the American Heart Association (AHA) 2020 guidelines for high-quality CPR. Thresholds for performance classification were defined by the Q-CPR software as follows:• Good performance: Overall quality score ≥ 95%• Average performance: Overall quality score between 85%–94%• Poor performance: Overall quality score < 84%

These thresholds are automatically applied by the Q-CPR software to categorize the rescuer’s performance after each simulation session. The score thus represents an integrated measure of compression quality that reflects adherence to recommended CPR parameters.

Secondary outcome measures included:•The impact of metronome guidance on maintaining optimal compression rhythm.•The difference in CPR performance between pretest and post-test phases within and between groups.

These outcome measures were chosen to comprehensively assess the effectiveness of metronome guidance in enhancing CPR quality among novice nurses.

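### The pre-test follows randomisation in an open-label trial, and the text does not exclude that the arm was already known, so the change-from-pre-test analyses are open to bias while the post-test comparison is not

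*Protocol article*

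**What the plan says.** All places are in the protocol article.

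- **Order.** Intervention and data collection: "Following randomization, all participants did a 2-minute pretest of compression-only cardiopulmonary resuscitation on a Q-CPR manikin without any metronome guidance". The same section gives the purpose of the pre-test as to "establish a baseline measurement of chest compression quality for both groups under identical conditions".
- **Allocation.** Randomisation, allocation concealment, and blinding: "As each participant enrolled in the study, they were asked to select a sealed envelope, which determined their group allocation". The concealment claimed there is that "neither the participants nor the researchers could predict group assignments prior to randomization", which covers the time up to randomisation and not the time between randomisation and pre-test.
- **Blinding.** Study design: "This was an open-label, two-arm, randomized controlled, single-center study". Intervention and data collection adds that "efforts were made to blind the data analysts to group assignments during the evaluation phase to minimize assessment bias". No blinding of participants or session staff at pre-test is described.
- **Use of the pre-test.** Data analysis plans a repeated measures ANOVA on rate, depth, recoil and overall performance, and paired t-tests within each arm. Outcome measures lists as a secondary outcome: "The difference in CPR performance between pretest and post-test phases within and between groups".
- **Analyses that do not use the pre-test.** Data analysis also plans independent t-tests between the arms at post-test, and a chi-square test for the post-test.

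The abstract and the specifications table describe the same two sessions and do not contradict this order.

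**The concern.** A baseline is protected by randomisation only if allocation cannot influence it. Here it is measured after allocation, in a trial that is not blinded. The manikin records compressions automatically, which removes rater bias, but compressing is voluntary and depends on effort. A nurse who knows that the metronome is coming, or that it is not, may pace or exert herself differently in the first session.

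The analyses at stake are those that subtract the pre-test. With two time points, the group-by-time test is the same as comparing mean change between the arms, so a difference in pre-test means caused by knowing the arm counts as if it were an effect of the metronome, with the sign reversed. Holding back in the metronome arm at pre-test would inflate the apparent benefit; trying harder would shrink it. The repeated measures ANOVA covers all four indicators listed as primary outcomes, and the article does not say which test carries the main conclusion.

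**Working it through.** **1. Sequence of events.** Enrolment and envelope selection, then a pre-test without metronome in both arms, then 20 minutes of rest, then a post-test with or without the metronome. The time at which the envelope was opened, or the arm became known to participant or staff, is not given.

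**2. Number per arm.** The Sample size section gives 72 per group before dropout and 10% dropout: 72/0.9 = 80, which matches the stated 80 per group. I use 80 per arm and a two-sided 0.05 level; the article gives 0.05 without stating sidedness.

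**3. Which tests take up a pre-test shift.** Let one arm's pre-test mean move by b SD, with no movement at post-test and no true effect.
- Group-by-time contrast (difference in mean change): biased by −b, in full.
- Paired t-test in the shifted arm: biased by −b, in full.
- Post-test independent t-test and chi-square test: no bias from this source, because the pre-test does not enter them.

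**4. Size, as an illustration.** The article gives neither b nor the pre-post correlation ρ, so both are assumed. With SD 1 at each test, the variance of one person's change is 2(1−ρ), and

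SE = √(2 × 2(1−ρ)/80)

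Rejection probability = Φ(b/SE − 1.96) + Φ(−b/SE − 1.96)

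For ρ = 0.5 and b = 0.2: SE = √(2/80) = 0.158 and b/SE = 1.26, so the rejection probability is 0.244.

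| ρ | SE | b/SE at b = 0.2 | Rejection, b = 0.1 | Rejection, b = 0.2 |
|---|---|---|---|---|
| 0.3 | 0.187 | 1.07 | 0.083 | 0.188 |
| 0.5 | 0.158 | 1.26 | 0.097 | 0.244 |
| 0.7 | 0.122 | 1.63 | 0.129 | 0.372 |

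The nominal rate is 0.05. With 72 per arm, the b = 0.2 figures are 0.174, 0.224 and 0.341.

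**5. Would adjusting for the pre-test cure it?** Only in part. In an analysis of covariance the bias is about ρb and the SE is √(1−ρ²) × √(2/80). For b = 0.2 the rejection probability is 0.068, 0.113 and 0.236 at ρ = 0.3, 0.5 and 0.7: lower than for change scores, but still above 0.05.

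**The case against.** The strongest reply is that early disclosure is not stated. Participants selected a sealed envelope; the text does not say that it was opened at once. The article is condensed, and its CONSORT figure is not available here. If the envelope stayed closed until after the pre-test, the problem disappears. This stands, and it limits the point to what the text fails to exclude.

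Other parts of the reply also stand:
- The phrase about identical conditions can fairly be read as the physical test: same manikin, same two minutes, no metronome in either arm. It is not shown to be false in that sense.
- A shift of equal size at both tests would cancel in the group-by-time contrast. The figures above require a shift at pre-test only.
- The direction is unknown, so some of the false positives could count against the metronome.
- A between-arm comparison free of the pre-test is already planned.

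A reader might infer something stronger: that the arm was known at pre-test, that staff coached the arms differently, or that the trial's estimated effect as a whole is biased. The documents do not support this. No time of disclosure is given, no coaching at pre-test is described, and the post-test comparisons do not depend on the pre-test.

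What the reply does not remove is the order itself. The article states that the pre-test came after randomisation and describes no safeguard for that interval. Automatic measurement and blinded analysts do not prevent a change in effort, and a later analysis plan cannot alter the sequence.

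**Conclusion.** The point holds as a risk of bias with a defined reach. The pre-test is a post-randomisation measurement, and the text does not rule out knowledge of the arm when it was taken. The group-by-time contrast, the paired t-tests and the secondary outcome on pre-post difference are exposed; the post-test independent t-test and chi-square test are not.

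Under assumed values, with 80 per arm, no true effect and a shift confined to one arm's pre-test, the false-positive rate of the group-by-time test is 19% to 37% for a 0.2 SD shift and 8% to 13% for a 0.1 SD shift, over correlations of 0.3 to 0.7. These figures show sensitivity and are not error rates of this trial, since neither the shift nor the correlation can be taken from the article. Because the time of disclosure is unstated and an unaffected comparison is already planned, this is something that should be fixed, held with medium confidence, and not a fatal flaw.

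**What to change.** **In the protocol as a procedure for others to repeat:** take consent, run the pre-test, then open the envelope (for example, during the 20-minute rest), then run the post-test. This needs no extra visit, test or staff; only the moment of opening moves.

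**For this trial:** the Study design section dates it November 2023 to March 2024 and 160 participants are reported as enrolled, so the order cannot now be changed. Instead:
- State when participants and session staff learned the allocation. If that was after the pre-test, this sentence settles the point.
- If it was before the pre-test, base the between-arm conclusion on the unadjusted post-test comparison that is already planned, and show any baseline-adjusted result beside it as a sensitivity analysis.
- In that case, also report the group-by-time and paired analyses as secondary and say that they are open to this bias.

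The cost is a sentence or two of text and at most one added sensitivity analysis, with no new data.
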